**Methods/design:**

A pragmatic, two-arm, randomized cluster controlled trial conducted in 22 community-based family practice clinics (36 clusters) with 76 fee-for-service family physicians in Winnipeg, Manitoba, Canada. Each physician will enroll 30 patients attending their periodic health examination and at average risk for colorectal cancer. All physicians will follow their standard clinical practice for screening. Intervention group physicians will provide a fridge magnet to each patient that contains information facilitating access to the study-specific colorectal cancer screening decision aids (telephone help-line and website). The primary endpoint is patient fecal occult blood test completion rate after four months (intention to treat model). Multi-level analysis will include clinic, physician and patient level variables. Patient Personal Health Identification Numbers will be collected from those providing consent to facilitate analysis of repeat screening behavior. Secondary outcome data will be obtained through the Clinic Characterization Form, Patient Tracking Form, In-Clinic Patient Survey, Post-Study Follow-Up Patient Survey, and Family Physician Survey. Study protocol approved by The University of Manitoba Health Research Ethics Board.

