## Methods/design

### Setting and participants

Family physicians will be recruited over a six month period from seven community areas (Figure 1) within the city of Winnipeg, Manitoba, Canada. Winnipeg is the capital city of the province with a population of approximately 685,000 (half the population of the province). In order to be eligible for the study, FPs must be in regular family practice (full or part-time), fee-for-service, solo or group practice and may be a member of the Physician Integrated Network and/or Uniting Primary Care and Oncology Network (Table 1). Once a family physician/medical clinic has agreed to participate in the study, a Family Physician/Clinic Characterization Form (Additional file 2) will be completed to document the routine care provided by each family physician in regards to CRC screening practices with the FOBT, whether they utilized an electronic medical record, have an on-site laboratory, and to document any additional information necessary to ensure minimal intrusiveness of the study protocol in the daily functioning of the clinical practice. Each family physician will enroll 30–35 patients who are: (1) attending their periodic health exam; (2) considered at average risk of developing colorectal cancer (Table 2); and (3) provide informed consent to participate. A patient tracking form (Additional file 3) will be filled out by the family physician for each patient enrolled.

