**Figure 1 F1:**
[figure not shown]
**The 12 community areas of Winnipeg, Manitoba, Canada. **The seven community areas represented in the study protocol include St. James-Assiniboia, Assiniboine South, Downtown, River Heights, St. Boniface, St. Vital, and Fort Garry. These represent those areas not yet involved in the province’s colorectal cancer screening program.

**Table 1 T1:** Description of stratification criteria Used in randomizing medical clusters to study groups

**Stratification criteria**	**Description**
**Physician Integrated Network (PIN) **[30]	A Manitoba Health primary care renewal initiative that focuses on fee-for-service (FFS) physician groups.
	Its goal is to facilitate systemic improvements in the delivery of primary care.
	Objectives:
	● To improve access to primary care
	● To improve Primary Care Providers’ access to and use of information
	● To improve the work life for all primary care providers
	● To demonstrate high quality primary care with a specific focus on Chronic Disease Management
**Uniting Primary Care and Oncology Network (UPCON)**[31]	A collaborative partnership between Winnipeg family practice clinics/primary health care centres and CancerCare Manitoba (CCMB) that is dedicated to promoting and supporting the shared care of the cancer patient.

**Table 2 T2:** Patient eligibility criteria

**Inclusion criteria**	**Exclusion criteria**
Attending for a Periodic Health Examination	Walk-in patients
Males and females 50 to 74 years of age	Having had a colonoscopy in the last 10 years
No symptoms of colorectal cancer	Having had a flexible sigmoidoscopy within the last 5 years
No personal history of CRC, polyps, or diseases of the colon requiring monitoring by colonoscopy (Crohn’s Disease or Ulcerative Colitis)	Having a double contrast barium enema within the last 5 years
Have a first degree relative with CRC affected at age greater than 60	
Have two or more second degree relatives with polyps or cancer	

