### Sample size determination, randomization, and statistical analysis

Individual randomization of physicians within a group-practice and individual patients to either the control or intervention arm of the study is not feasible [32]. A cluster randomized design was chosen in which family physicians within a group practice were randomized to the same experimental group (control or intervention) and considered a cluster. Randomization of clusters will be conducted by a biostatistician using a computer-generated list and all of a physician’s patients will receive the same experimental treatment (control or intervention). Our protocol defines a multi-level analysis facilitating analysis of the intraclass correlation coefficient (ICC) for each primary group-level outcome (patients, FP, clinics/clusters) [32]. To ensure an even distribution of cluster-level characteristics between experimental groups, clusters will be randomized within strata based on membership in the Physician Integrated Network (PIN) and/or Uniting Primary Care Oncology Network (UPCON) [28]. These represent two quality improvement initiatives in Manitoba (Table 2). Clusters will be block randomized based on the number of collaborating FPs within a practice. An absolute increase in FOBT screening rates of 15% from the current 42% in Manitoba will be considered clinically significant [14]. Sample size was determined by a biostatistician using PASS (Power and Sample Size, 2002) software and a computer simulated ICC value of 0.6 [33] taking into consideration the clustered design of the trial [34]. This is a very conservative estimate of the minimum detectable effect size (MDEF) given the proposed sample size. Based on logistic regression a cluster size of 41 clusters each enrolling 30 to 35 patients (of which 80% are in the group that does not utilize the supplied intervention/magnet and 20% are in the group that does utilize the intervention/magnet; 1230 observations) will achieve 90% power at a 0.05 significance level to detect a change from the baseline value of 0.400 to 0.550 and corresponds to an odds ratio of 1.833. In the event that family physician collaboration/retention and/or patient recruitment proves to be more difficult than anticipated, a logistic regression with a cluster size of 28 (840 observations) achieves 80% power with the same outcomes.

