### Description of the study protocol

This study protocol was approved by The University of Manitoba Health Research Ethics Board (Additional files 7, 8, 9 and 10) and is outlined in detail in Figures 4, 5, 6 and Tables 3–4. Table 5 provides an outline of and link to the study protocol forms and surveys along with a summary of the information obtained from each and the anticipated number of responses. Table 6 provides a description of the contents of the study set-up package. Upon arrival for their periodic health examination, eligible patients (Table 2) in both study groups will be asked by medical clinic support staff to complete the In-Clinic Patient Survey. This survey provides an explanation of the study and asks the patient to respond to a few general questions related to colorectal cancer screening, computer use for health-related questions, and permission to be contacted for the follow-up survey. It will function as the patient consent form. A business card will be attached to each In-Clinic Patient Survey providing the telephone numbers for the University of Manitoba Health Research Ethics Board and the Study Coordinator to facilitate patient contact as necessary. Patients declining to answer the survey return it to the clinic support staff who document that the patient declined to participate. Those patients completing the In-Clinic Survey will bring it with them and gave it to their FP during their periodic health examination. The FP will determined patient eligibility. All FPs conduct CRC screening as per their standard clinical practice. If a patient is ineligible, the FP will not enroll the patient. If the patient is eligible, the FP will enroll the patient by filling out a Patient Tracking Form. FPs will have a Patient Tracking Form Binder containing a Patient Tracking Form for each eligible patient in each of their evaluation rooms. Each Patient Tracking Form will have a removable sticker with the unique study identification number on it. The FP will remove and affixed this sticker to the patient’s In-Clinic Survey. Patients will be given four months to complete their FOBT. FPs in the intervention group will provide each eligible patient with a refrigerator magnet (paper clipped to the corresponding Patient Tracking Form). The protocol design allows us to determine how many patients provided with the magnet called the telephone support line as well as the number of times they called and their most common questions. It also allows us to determine which patients accessed the website, the pages they visited, and the information they were most interested in. Approximately four months after the last patient is enrolled, each FP will be provided with a list of their enrolled patients on which they will document the date of FOBT completion for those patients completing the test or an incomplete (for those not completing the FOBT). Patient FOBT results will not be collected. Using a computer generated randomization list, 10 patients per FP who agreed to be contacted for the Post-Study Follow-Up Survey will be contacted via telephone to complete the survey.

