**Figure 6 F6:**
[figure not shown]
**Flow diagram of intervention group study protocol for family physicians and support staff. *** Family Physicians will complete the Family Physician Survey upon completion of study requirements. Please refer to text for further details.

**Table 3 T3:** Study protocol steps for control group

**Study protocol step**	**Description/details of study protocol step**
**STEP #1**	Patients between the ages 50–74 report to the reception desk/support staff for their Periodic Health Examination (PHE) or regular visit in which the family physician determines there is an opportunity for colorectal cancer screening (Fecal Occult Blood Test; FOBT).
**STEP #2**	Support staff provide patients meeting the above criteria with the In-Clinic Patient Survey (found in the study binder marked In-Clinic Patient Surveys) on a clipboard.
**STEP #3**	Patient decides whether they will fill out the In-Clinic Survey.
	If a patient declines to fill out the In-Clinic Survey, the support staff documents the patient’s age, gender, and reason(s) they declined to fill out survey (on the back of the In-Clinic Survey). Please clip the survey to the front of the study binder marked In-Clinic Patient Surveys.
	If a patient fills out the survey, they take it with them and give it to their family physician at the beginning of their appointment. The clipboard is returned to support staff so they are able to use it for the next patient.
**STEP #4**	The patient gives their In-Clinic Patient Survey to their family physician at the beginning of their appointment.
**STEP #5**	The family physician takes the In-Clinic Survey from the patient and determines if they are eligible for the study based on the inclusion/exclusion criteria found at the front of the family physicians study binder marked Patient Tracking Forms.
	If patients are ineligible, clip the In-Clinic Survey to the front of study binder marked Patient Tracking Forms.
	If patients are eligible:
	Turn to an unused Patient Tracking Form in the study binder. Record the date, the patient’s NAME, and mark the checkbox indicating the method of FOBT distribution to the patient.
	Remove the study ID number sticker from the Patient Tracking Form and place it on the patient’s In-Clinic Survey.
	Clip the In-Clinic Survey to the front of the Study Binder.
	Proceed with colorectal cancer screening with the Fecal Occult Blood Test (FOBT) as per usual clinical practice.

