**STEP#6**	Study coordinator ([name]) will arrange a convenient date to collect forms and determine those completing their FOBT. In the event that you require more In-Clinic Surveys or have a question/comment/concern, please contact [name] at [name] or [contact]

**Table 4 T4:** Study protocol steps for intervention group

**Study protocol step**	**Description/details of study protocol step**
**STEP #1**	Patients between the ages 50–74 report to the reception desk/support staff for their Periodic Health Examination (PHE) or regular visit in which the family physician determines there is an opportunity for colorectal cancer screening (Fecal Occult Blood Test; FOBT).
**STEP #2**	Support staff provides patients meeting the above criteria with the In-Clinic Patient Survey (found in the study binder marked In-Clinic Patient Surveys) on a clipboard.
**STEP #3**	Patient decides whether they will fill out the In-Clinic Survey.
	**If **a patient declines to fill out the In-Clinic Survey, the support staff documents the patient’s age, gender, and reason(s) they declined to fill out survey (on the back of the In-Clinic Survey). Please clip the survey to the front of the study binder marked In-Clinic Patient Surveys.
	**If **a patient fills out the survey, they take it with them and give it to their family physician at the beginning of their appointment. Clipboard is returned to support staff so they are able to use it for the next patient.
**STEP #4**	The patient gives their In-Clinic Patient Survey to their family physician at the beginning of their appointment.
**STEP #5**	The family physician takes the In-Clinic Survey from the patient and determines if they are eligible for the study based on the **inclusion/exclusion criteria found at the front of the family physicians study binder marked Patient Tracking Forms.**
	If patients are **ineligible**, clip the survey to the front of Study Binder
	If patients are **eligible**:
	Turn to an unused Patient Tracking Form in the Study Binder and record the **date,** the **patient’s NAME,** and mark the **checkbox** indicating the method of FOBT distribution to the patient.
	Remove the study ID number sticker from the Patient Tracking Form and place it on the In-Clinic Survey.Remove study magnet from Patient Tracking Form and give it to the patient. Clip the In-Clinic Survey to the front of the Study Binder.

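### Two conflicting visit rules govern eligibility, and the wider one lets physicians who already know their arm judge which regular visits count

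*Protocol article*

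**What the plan says.** **Periodic examination only.** The Abstract's methods paragraph states "Each physician will enroll 30 patients attending their periodic health examination and at average risk for colorectal cancer". Setting and participants lists as its first enrolment condition "(1) attending their periodic health exam". The first inclusion criterion in Table 2 is "Attending for a Periodic Health Examination", and its exclusions include "Walk-in patients". Description of the study protocol also starts from the patient's arrival for that examination.

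**Periodic examination or another visit.** Step 1 of Table 3 (control) extends the entry point with "or regular visit in which the family physician determines there is an opportunity for colorectal cancer screening". Step 1 of Table 4 (intervention) carries the same clause, "regular visit in which the family physician determines there is an opportunity for colorectal cancer screening".

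**Who enrols, and when.** Clusters are randomised, and all of a physician's "patients will receive the same experimental treatment (control or intervention)" (Sample size determination, randomization, and statistical analysis). Support staff hand out the In-Clinic Patient Survey, which also serves as the consent form. The physician then applies the criteria in the study binder (Step 5), and "If the patient is eligible, the FP will enroll the patient by filling out a Patient Tracking Form". In the intervention arm the magnet is attached to that form.

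**What is recorded and modelled.** Tables 3 to 6 list date, patient name and kit distribution method for the Patient Tracking Form. The patient-level variables in the model are age, gender, socioeconomic status and previous FOBT history. Visit type is in neither list.

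**The concern.** Table 2 is an objective rule: the booked visit is a periodic examination or it is not. Step 1 of Tables 3 and 4 adds a second route that depends on the physician's judgement of the visit. Clinics following the steps could admit patients whom Table 2 bars. Clinics could also differ in how they resolve the conflict.

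The timing makes this more than an editing slip. In a cluster trial that recruits after allocation, randomisation balances clusters, not the patients who later enter them. If the person applying a subjective entry rule knows the arm, patients can differ between arms before anyone uses the telephone line or website. Intention to treat keeps enrolled patients in their allocated arm, but it does nothing about who was enrolled. The Limitations section discusses which physicians join the study, not which patients physicians enrol after allocation.

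Visit type could plausibly matter for completion. In the Manitoba survey cited in the Background, 79% gave a routine check-up or screening as a reason for having done the test. That figure does not compare completion by visit type, so it suggests a link without measuring one. If visit type is not recorded at enrolment, the analysis may not be able to recover it later.

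**Working it through.** **1. The passages side by side**

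| Place | Visit that qualifies |
|---|---|
| Abstract, methods | Periodic examination |
| Setting and participants | Periodic examination |
| Table 2 | Periodic examination; walk-ins excluded |
| Description of the study protocol | Periodic examination |
| Table 3, Step 1 | Periodic examination, or a regular visit the physician judges suitable |
| Table 4, Step 1 | Same as Table 3 |

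Step 5 refers back to the binder criteria. If the binder repeats Table 2, a regular-visit patient is let in at Step 1 and barred at Step 5. If it does not, Table 2 is not the operating rule. Condensing a longer protocol does not explain this, because both rules are printed.

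**2. The route to selection**

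- Allocation comes before patient enrolment and applies to the whole cluster.
- The physician decides eligibility and enrols.
- The intervention physician knows the arm, because the magnet is on the form. Control physicians work from a separate instruction table without a magnet.
- The regular-visit clause is the one entry condition expressed as the physician's own judgement.

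**3. Scale, for illustration only**

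The article gives no figure on this point, so there is none to reproduce. Let f be the excess share of one arm's places that go to selectively enrolled patients, and d their excess completion probability. Both are assumptions. The shift in the arm difference is f × d, in percentage points:

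| f | d = 0.10 | d = 0.20 | d = 0.30 | d = 0.40 |
|---|---|---|---|---|
| 0.05 | 0.5 | 1 | 1.5 | 2 |
| 0.10 | 1 | 2 | 3 | 4 |
| 0.20 | 2 | 4 | 6 | 8 |

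For example, 0.05 × (0.80 − 0.40) = 0.02 and 0.10 × (0.80 − 0.40) = 0.04. With 30 places per physician, 10% is 3 patients. Against the 15-point difference the article calls clinically significant, 2 points is 2/15 = 13% and 4 points is 4/15 = 27%.

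**4. Effect on a null comparison**

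Assume no true effect, a completion rate of 0.40, and the article's 1230 observations split equally (615 per arm). The design effect is 1 + (30 − 1) × ICC. The standard error is √(2 × 0.40 × 0.60 / n), with n = 615 / design effect. The table gives the rejection rate of a two-sided 5% test by normal approximation:

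| ICC | Design effect | n per arm | SE | Shift of 2 points | Shift of 4 points |
|---|---|---|---|---|---|
| 0.05 (assumed) | 2.45 | 251.0 | 0.0437 | 7.4% | 15.0% |
| 0.10 (assumed) | 3.90 | 157.7 | 0.0552 | 6.5% | 11.2% |
| 0.6 (article's value) | 18.4 | 33.4 | 0.1198 | 5.3% | 6.3% |

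At the article's ICC the error rate barely moves, because the comparison would then be very imprecise. The shift in the estimate is the same in every row.

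**The case against.** Much of the opposing case stands.

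- **A reader might infer that any visit qualifies.** It does not. The clause is limited to regular visits, Table 2 excludes walk-ins, and Step 5 still applies the binder criteria.
- **A reader might infer that physicians may pick whom they like.** The article does not say so. Staff approach patients, consent comes first, and eligible patients are to be enrolled. Discretion enters through the regular-visit clause. An explicit consecutive-enrolment rule may also be in the full protocol, which is not shown.
- **A reader might infer that the intention-to-treat estimate is biased.** The clause is identical in both arms, so it is not differential in itself. Bias would arise only if physicians used it differently by arm. No motive specific to one arm is documented: the honorarium depends on the number of physicians, and completion rates are fed back to all of them. An unblinded physician could also select patients under Table 2 alone.
- **The planned adjustment helps.** Previous FOBT history probably captures part of a patient's willingness to test. The shifts above make no allowance for it.

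None of this reconciles Table 2 with Step 1. Nor does it remove the fact that a judgement-based entry condition is applied by someone who knows the allocation, with nothing recorded that would show afterwards how it was used.

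**Conclusion.** The eligibility contradiction is established from the text and needs correcting. The selection risk follows from three documented features: enrolment after allocation, physicians who know their arm, and a discretionary clause. Its size is unknown. The 2 to 4 point shift is only an illustration. It assumes that selection happens in one arm alone, that 5% to 10% of places are affected, and that completion is 80% rather than 40% in those patients. The article supports none of these values.

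A reader might also compare such a shift with a smaller effect, diluted by low use of the aids, and conclude that bias could account for the whole result. The article states no such target. Its only stated benchmark is 15 points, and against that the illustration amounts to 13% to 27%.

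**What to change.** 1. Reconcile Table 2, the matching text and Step 1 of Tables 3 and 4 to one objective visit definition, identical in both arms. Whether regular visits belong in it is for the investigators to decide.
2. State that every consenting patient who meets the listed criteria is enrolled consecutively until the physician reaches 30 to 35.
3. Add a visit-type tick box to the Patient Tracking Form.
4. Report enrolled, ineligible and declined counts by arm. Compare age and gender in all three groups. Compare previous FOBT history only among patients who completed the survey, because staff record only age, gender and reason for those who decline.
5. If regular visits are kept, adjust for visit type or run a sensitivity analysis in periodic-examination patients.

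Items 4 and 5 have limits. Retained surveys cannot reveal eligible patients who were never offered one, and an analysis confined to periodic examinations would miss selection within them. Item 2 is therefore the main protection. The cost is revised wording in the protocol and binders, one extra form field, and possibly slightly slower enrolment.
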